## Abstract

**Introduction:**

Polypharmacy in patients with advanced cancer represents a major public health problem, leading to risk of iatrogenesis, decrease of quality of life and increase of healthcare costs. In the field of geriatrics, health policies have been developed to address polypharmacy through the use of deprescribing tools. Recently, palliative care initiatives have been introduced, yet these have not fully considered the specificities of this population, particularly their perceptions. It is therefore important to better understand patients’ perceptions of deprescribing in order to adapt tools and actions to make these approaches more effective.

**Objectives:**

The aim is to investigate patients’ perceptions of deprescribing in palliative oncology care, and to explore factors that may influence patients’ attitudes and beliefs about deprescribing and to validate a specific questionnaire (rPATD) in this population. An ancillary study will investigate the relationship between patients’ health literacy and their perception of deprescribing.

**Method:**

A prospective, observational, multicenter study will be conducted using a sequential mixed exploratory design in a population of patients living with advanced cancer and with a physician-estimated life expectancy of less than 1 year. The study will include an initial qualitative phase. Individual semi-structured interviews using a descriptive approach (thematic analysis) will be conducted (upon saturation). Following analysis of the qualitative data, a quantitative study including 300 patients will be realized to meet secondary objectives. Several data will be collected and 2 self-questionnaires will be administered: the BMQ (beliefs about medicine) and rPATD (perception of deprescribing) possibly supplemented by additional items if required by the qualitative analysis. The auxiliary study will be conducted during this second phase, using a validated self-questionnaire to assess patients’ level of literacy.

**Conclusion:**

The disparate outcomes will facilitate the understanding of the perception of deprescribing in palliative oncology care, enabling the development of tailored approaches adapted to this population.

**Trial registration:**

**ClinicalTrials Identifier**: NCT06193083.

## Introduction

### Polymedication in palliative care

Polymedication is defined by the World Health Organisation as the administration of several drugs at the same time or the administration of an excessive number of drugs [1]. It is a common phenomenon in patients suffering from serious, life-threatening and incurable illnesses [2, 3], with the average number of prescribed medications per patient ranging from 3 to 23 [3]. However, polymedication can be associated with reduced quality of life and an increased risk of iatrogenicity [2, 4], which increasingly leads clinicians to limit drugs to those that are necessary for the patient. Some prescribed drugs can be considered as inappropriate for patients (PIMs—Potentially Inappropriate Medications) due to their age, state of health or co-morbidities. This may result in adverse effects or potentially dangerous drug interactions. In international studies conducted in palliative care, the prevalence of patients with at least one potentially inappropriate prescription is reported to range from 15% to 92% [3].

### Deprescribing and palliative care

Deprescribing is currently a crucial issue in medicine. It is defined as the process of reducing or stopping the use of a drug or drug treatment because of its ineffectiveness, inappropriateness, adverse effects, dangerous drug interactions or according to patient preference. This approach also aims to optimize drug therapy by reducing the risks and costs associated with unnecessary or inappropriate drug treatments [2, 5].

To date, international deprescribing policy has focused mainly on the elderly. However, in recent years there has been debate about adapting this policy to the palliative care population [4, 6], especially for advanced cancer patients, who are at higher risk of multiple drug interactions [4, 7, 8], especially with cancer-specific treatments [9]. Deprescribing in palliative oncology care requires individualized care, since uncontrolled symptoms and adverse effects can appear after stopping treatments [10]. Careful planning and clear communication between healthcare professionals, patients and caregivers are needed to promote effective, safe and accepted deprescribing [11].

In light of these concerns, tools have been developed to assist physicians in the process of deprescribing [12]. For instance, the STOPPFrail 2 tool [13] (in S1 File) aims to identify whether a patient is taking PIMs. It has been validated in a geriatric population with an estimated life expectancy of less than one year, and is not specific to oncology. In the context of oncology palliative care, the OncPal tool has been developed to identify PIMS in patients with a life expectancy of less than 6 months [14]. To our knowledge, no tool has been developed to identify PIMs in cancer patients with more than 6 months of life expectancy. In addition, there is a lack of tools to assess how deprescribing is perceived by cancer patients, while the rPATD tool assesses patients’ beliefs and attitudes regarding deprescribing in the geriatric population [15].

Few studies have examined the perceptions of deprescribing among cancer patients [16, 17]. Results from a study on the cessation of statins [17] suggest that palliative care patients may not be concerned about the consequences of stopping their preventive treatments. However, for some patients, it can be challenging to question the discontinuation of a “lifelong” treatment, as it may cast doubt on the rest of their lives. They may interpret it as an imminent death.

Physicians themselves may be reluctant to suggest treatment discontinuation and its consequences for patients [18]. Consequently, further research in this area is required to better support deprescribing in palliative care, which is an integral part of care and can help to improve patients’ quality of life [10]. It seems necessary to better understand patients’ perceptions of deprescribing, in particular for potentially inappropriate drugs, in order to adapt support to each patient. Indeed, we believe that these elements can be influenced by the health literacy of our patients, defined as the ability to acquire, understand and use information in ways that promote and maintain good health [19]. To date, and to the best of our knowledge, no study has yet investigated this hypothesis.

The main aim of our study will be to describe patients’ attitudes and beliefs towards deprescribing, using a patient-centered approach. As secondary objectives, the factors that may influence patients’ attitudes and beliefs regarding deprescribing will be studied, and the rPATD will be adapted and validated in this population. Finally, the relationship between patients’ level of health literacy and their perception of deprescribing will be examined.

## Methods

### Study design

A prospective, observational, multicenter study will be conducted using a sequential mixed exploratory design in a population of patients living with advanced cancer and with a physician-estimated life expectancy of less than 1 year.

The study will include an initial qualitative phase concerning patients’ attitudes and beliefs towards deprescribing. Individual semi-structured interviews using a descriptive approach will be conducted. Following the analysis of the qualitative data, a quantitative study will be conducted to understand the factors that may influence patients’ attitudes and beliefs regarding deprescribing. This will be achieved through the use of questionnaires that explore two keys areas: *(I)* patients’ representations of medicine (BMQ) and *(II)* patient’s perception of deprescribing. The rPATD questionnaire may be adapted depending on the results of the qualitative study. The psychometric properties of the rPATD in this population will then be studied to validate this tool.

During this second phase, an ancillary study will be conducted based on voluntary patient participation to investigate the relationship between the patients’ level of health literacy and their perception of deprescribing.

### Study setting and scientific committee

This multicenter study will be conducted in oncology and/or palliative care departments of hospitals located in western France. In this geographical area, all 5 oncology/ palliative care centers are participating.

The scientific committee of this study is a multidisciplinary team of clinicians and researchers, comprising pharmacists, pharmacologists, physicians, biostatisticians and psychologists. They are interested in the patient-centered approach and the proper use of medication. They supervise all phases of the studies, from methodological choices to the analysis and interpretation of results. For each phase (qualitative and quantitative), there are experts in each methodology.

### Population

The study will be introduced to adult patients with advanced "solid" cancer who have at least one PIM, followed either as inpatients or outpatients, and whose life expectancy is estimated by the physician to be less than one year.

### Inclusion criteria

Patients over 18 years oldLocally advanced or metastatic solid cancer (i.e., palliative care as defined by the World Health Organization [20])Life expectancy estimated by the physician at inclusion of less than 1 year (will be estimated by the attending physician’s surprise question:"Would you be surprised if your patient died within a year?" [21–23]).Hospitalised (whether in conventional hospitalization or in a day hospital) or in consultationWith at least one PIM (identified using STOPPfrail 2) [13] (in S1 File). This is a tool developed in geriatrics, validated for a population with an estimated life expectancy of less than one year, and is not specific to oncology.Patient not having expressed opposition to participating in the study after receiving information from the physician.

And for patients in the qualitative study:

Patient having signed the authorization to have their voice recorded during the semi-structured interview for written transcription.

### Non-inclusion criteria

Major under guardianship, protected personPatient unable to speak or write FrenchPatients with impaired judgment, cognitive or sensory impairments preventing them from receiving informed information, answering questionnaires or participating in study interviews.

### Second part of our mixed study: Quantitative phase

Once the conclusions of the qualitative study have been drawn (depending on the results of the qualitative study, items not included in the rPATD may be added), a quantitative study will be conducted (including 300 patients).

In order to meet our **main objective** (investigating the perception of deprescribing held by patients in palliative cancer care), we will describe the distribution of rPATD scores (and potentially added items not present in rPATD) in our sample. The rPATD is a patient self-questionnaire that has been validated and adapted in French [15] (in S3 File) to assess patients’ perceptions of their treatments and deprescribing. It is available for use without license. The questionnaire comprises 22 questions, which are assessed on a 5-point Likert scale. It includes two questions on overall satisfaction with medication use and willingness to accept deprescribing recommendations, as well as 20 questions grouped into four validated factors: (I) perceived drug burden (Burden factor), (II) attitudes towards the appropriateness of prescribed medications (Relevance factor), (III) concerns about stopping medications (Concerns about stopping medications factor), and (IV) participants’ level of knowledge about their medications and their degree of involvement in the medication decision-making process (Involvement factor). The instrument was initially employed in the geriatric population, but recent studies have utilised it in adult patients of all ages [28–30].In order to meet **secondary objective 1** (studying factors that may influence patients’ attitudes and beliefs regarding de-prescribing), a linear model will be employed to explain the rPATD questionnaire scores by the various covariates collected. These include the sex, age, highest level of education, type of cancer (by major primary site), number of months since cancer onset, number of metastatic sites, performance status [31] at inclusion, presence of systemic cancer treatments (chemotherapy, targeted therapy, immunotherapy, hormone therapy…), presence of follow-up by palliative care team, patient’s place of care (hospitalization, home, nursing home…), number of medications (number of different molecules prescribed and taken by the patient), number of PIMs (using the STOPPfrail 2 tool [13]), the physician’s estimate of the patient’s life expectancy at 3 and 6 months (using the surprise question "Would you be surprised if your patient died within 3 months?") [21–23], person in charge of medication management (patient, caregiver) and patient’s beliefs about treatments in general. For the latter, the Beliefs about Medicine Questionnaire (BMQ) will be utilized. The BMQ is a 18-item self-administered questionnaire, designed to explore patients’ representations of medicine (in S4 File). It is validated in French [32] with license-free use. Ten items concern specific beliefs about prescribed treatments (the need to take a treatment to stay healthy items 1, 3, 4, 7, 10) and fear of treatment-related risks items 2, 5, 6, 8, 9). Furthermore, eight items concern general beliefs (the idea that physicians overuse medicines items 11, 14, 17, 18 and fear of potential danger associated with medication in general items 12, 13, 15, 16). A 5-point Likert-type scale was used for each item, with higher scores indicating stronger beliefs.In order to meet the **secondary objective 2** (validating the rPATD in this population by evaluating the psychometric properties of the rPATD in this population), a confirmatory factor analysis (CFA) will be performed on the rPATD items. The structure of the rPATD will be deemed coherent if the CFI value is greater than 0.9. and the RMSEA value less than 0.08. The reliability will be considered good if Cronbach’s alpha value is greater than 0.7 for each dimension. Concurrent validity will be considered to be good if Spearman correlations between rPATD scores and BMQ questionnaire scores are significant.

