#### Concerning our sample size

With regard to the qualitative part, the saturation of themes during analysis is a determining factor. As stated by Braun and Clarke [34], the sample size cannot be determined in advance.

With regard to the quantitative phase, the literature indicates that this type of descriptive quantitative methodology is carried out on a fairly large patient population, generally 300 to 400 patients [39, 42]. It is challenging to determine the requisite number of subjects in this study, as there is no primary hypothesis to be tested. However, it is crucial to have sufficient data to identify potential influencing factors with sufficient statistical power. Therefore, we anticipate 300 subjects in this part of the study.

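### Concurrent validity of the rPATD is judged by statistical significance alone, so at n = 300 correlations of about 0.113, of either sign, could earn the label good

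*Protocol article*

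**What the plan says.** The protocol article, under the Quantitative phase heading, gives three decision rules for secondary objective 2, the validation of the rPATD in this population.

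- **Structure:** confirmatory factor analysis, with CFI above 0.9 and RMSEA below 0.08.
- **Reliability:** Cronbach's alpha above 0.7 in each dimension.
- **Concurrent validity:** "Concurrent validity will be considered to be good if Spearman correlations between rPATD scores and BMQ questionnaire scores are significant".

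The same section describes the scores involved. The rPATD has two global questions and "20 questions grouped into four validated factors". For the BMQ, "Ten items concern specific beliefs about prescribed treatments", split into necessity and fear of treatment-related risks, and "eight items concern general beliefs", split into overuse and potential danger. That makes four BMQ subscales.

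On size, "a quantitative study will be conducted (including 300 patients"), and the sample-size discussion repeats the figure: "Therefore, we anticipate 300 subjects in this part of the study". That discussion calls the required number hard to determine "as there is no primary hypothesis to be tested". No significance level or sidedness is given for the correlations.

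**The concern.** Evidence of concurrent validity lies in how strongly two instruments agree and in whether they agree in the expected direction. A significance test of rho answers neither question. It asks whether rho could be zero, and the answer depends on the number of patients as well as on the correlation. In a sample of 300, a correlation too weak to support any claim of validity can be significant, and so can one that runs opposite to theory.

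The rule also does not say how many correlations must be significant. That choice could be made after the results are seen.

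At stake is one of the three labels on which the validation claim would rest. The article's discussion of the questionnaires says that none is validated for this population, so later users may rely on what this study reports.

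**Working it through.** **Inputs from the article.** n = 300; four rPATD factors; four BMQ subscales; hence up to 4 × 4 = 16 correlations.

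**Assumption.** Two-sided 5%, because the article gives no level. Alternatives are shown in step 2.

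**Plan's own figure.** The article states no critical or minimum correlation, and n = 300 comes from custom rather than a formula, so there is nothing to reproduce.

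**1. Smallest significant correlation.** r_crit = t / √(n − 2 + t²). With t = 1.968 on 298 df, r_crit = 1.968 / √(298 + 3.873) = 0.1133. Shared rank variance is 0.1133² = 0.0128, about 1.3%. Checks: z/√(n − 1) gives 0.1133, and the simulated permutation distribution of Spearman's rho gives 0.1130. Fisher's z with the Spearman variance 1.06/(n − 3) gives 0.1166.

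**2. Sensitivity of the threshold.**

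| Assumption | Smallest significant \|rho\| |
|---|---|
| One-sided 5%, n = 300 | 0.095 |
| Two-sided 5%, n = 300 | 0.113 |
| Two-sided 1%, n = 300 | 0.149 |
| Bonferroni over 16 (0.05/16 = 0.003125), n = 300 | 0.170 |
| Two-sided 5%, 270 complete questionnaires | 0.119 |
| Two-sided 5%, 240 complete questionnaires | 0.127 |

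**3. How often a weak true correlation is significant.** Fisher's z with SE = √(1.06/297) = 0.0597.

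- True rho 0.15: atanh(0.15)/0.0597 = 2.53, and Φ(2.53 − 1.96) = 0.72.
- True rho 0.20: atanh(0.20)/0.0597 = 3.39, and Φ(3.39 − 1.96) = 0.92.

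**4. If one significant correlation out of 16 were enough.** With every true correlation zero and the tests independent, the chance of at least one is 1 − 0.95¹⁶ = 0.56. In simulation with an assumed correlation of 0.3 between the scores within each instrument, it is about 0.50.

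**5. If all 16 were required.** The result depends on the true values. With independence and every true rho at 0.20, the chance of passing is 0.924¹⁶ = 0.28. With every true rho at 0.30, it is 0.9994¹⁶ = 0.99. Each correlation would still need only about 0.113.

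**6. Whether n = 300 can carry a magnitude criterion.** Taking 0.30 as an illustrative cut-off, an observed rho of 0.30 has 95% CI tanh(0.3095 ± 1.96 × 0.0597) = 0.19 to 0.40. If the true rho is 0.40, the chance of observing at least 0.30 is Φ((0.4236 − 0.3095)/0.0597) = Φ(1.91) = 0.97.

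**The case against.** Four objections deserve an answer.

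- **The rest may be in the SAP.** A condensed article may leave named pairs, expected signs, the significance level and multiplicity to the full protocol or the SAP, and their absence alone is no finding. That stands. But the article does state the criterion for calling concurrent validity good, and that criterion is significance. It gives magnitude cut-offs for the two neighbouring criteria, so brevity does not explain the difference.
- **The plural.** The rule says "Spearman correlations between rPATD scores and BMQ questionnaire scores are significant", not that any single one suffices. A reader might infer that one significant pair is enough, but the text does not say so, and the 50 to 56% figure applies only on that reading. Nor do the documents support the opposite inference, that requiring all 16 would be almost impossible: step 5 shows a wide range, and no passage says which factors should be unrelated to which subscales. What stands is that the rule is undefined.
- **The scope.** A reader might infer that a correlation of 0.11 would validate the questionnaire. It would not. At n = 300 an observed rho of exactly 0.110 gives two-sided p = 0.057 and is not significant. Passing would earn only the concurrent-validity label, since structure and reliability are judged separately by size.
- **The comparator is established.** The article notes that the BMQ was used in the original rPATD validation and in translations. That supports the choice of instrument but does not make a p-value a measure of validity.

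**Conclusion.** The concern holds in a limited form. The stated rule can label concurrent validity good on correlations that are negligible or run the wrong way. The threshold is about 0.113 at n = 300 under an assumed two-sided 5% level, and it stays weak (0.095 to 0.170) under the other levels considered. Whether one, some or all of the correlations must reach it is not defined.

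The consequence is bounded. This is one of three criteria for a secondary objective in an observational study whose main objective is descriptive. If the coefficients are reported, readers can judge their strength for themselves. It should be fixed before analysis, but it is not a fatal flaw.

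**What to change.** Before data lock, replace significance with a criterion of size and direction:

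1. Name the rPATD factor and BMQ subscale pairs expected to correlate, with the expected sign of each.
2. Set a minimum |rho| and justify it. A value of 0.30 is offered as an example; it is not taken from the documents.
3. State how many of the named pairs must meet both the sign and the minimum.
4. Report every rho with its 95% CI, and treat p-values as descriptive.

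The cost is one paragraph in the protocol or SAP, with no new patients or data. The downside is that the criterion can fail. Take one named pair per factor, a cut-off of 0.30 on point estimates and a requirement of at least 3 of 4 pairs. If every true rho is exactly 0.30, each pair passes with probability about 0.5, and the whole criterion passes with probability 4 × 0.5⁴ + 0.5⁴ = 5/16, about 31% (independence assumed). If the true rho is 0.40, each pair passes with probability about 0.97. The cut-off and the required count should be chosen with these rates in view.

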
#### Ancillary study

In order to meet the **objective of the ancillary study** (investigating the relationship between patients’ level of health literacy and their perception of deprescribing), we will calculate the Spearman correlation coefficients between the rPATD scores and the FCCHL/HLS14 scores. The FCCHL (Functional, Communicative and Critical Health Literacy) / HLS14 (14-item health literacy scale) (in S5 File) is self-administered questionnaire [33], validated in French. It is available without a license and comprises 14 items with a 5-point Likert scale to assess health literacy [34] which can be categorized as functional literacy, communicative or interactive literacy, and critical literacy.

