#### Concerning the choice of an ancillary study

As previously stated, we have deliberately chosen to leave patients free to participate in this complementary study, to avoid the principal study being perceived as too burdensome by our often tired patients. This is why we refer to it as an auxiliary study, given that the questionnaire is not systematic. This choice introduces a population selection bias, but the risk of the study appearing too burdensome seems to us to outweigh this bias. The objective is simply to obtain preliminary results that will provide information for future studies on the link between the level of health literacy and patients’ understanding of the phenomenon of deprescribing.

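### The ancillary literacy question is answered only by crude Spearman correlations in volunteers, although covariates planned for the whole quantitative phase would allow an adjusted estimate beside them

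*Protocol article*

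**What the plan says.** The Ancillary study section of the protocol article states the method: "we will calculate the Spearman correlation coefficients between the rPATD scores and the FCCHL/HLS14 scores". It mentions no adjustment.

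Study design says that "an ancillary study will be conducted based on voluntary patient participation". The Discussion section on the choice of an ancillary study explains the label: "given that the questionnaire is not systematic". The same section acknowledges the consequence and accepts it: "This choice introduces a population selection bias, but the risk of the study appearing too burdensome seems to us to outweigh this bias". It also limits the ambition: "The objective is simply to obtain preliminary results that will provide information for future studies".

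The Introduction (Deprescribing and palliative care) gives the motive, a hypothesis that the authors say is untested: "we believe that these elements can be influenced by the health literacy of our patients".

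The Quantitative phase section plans 300 patients. For secondary objective 1 it plans a linear model for the rPATD scores. The listed covariates include sex, age, highest level of education and performance status. Literacy is not on the list. No section connects these covariates to the ancillary analysis or plans a comparison of patients who complete the literacy questionnaire with those who do not.

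**The concern.** The hypothesis concerns influence, but the stated analysis describes only a marginal association. Education and age are plausible common causes of literacy and of attitudes to medicines. The protocol itself lists both as candidate determinants of the rPATD scores, then leaves them out of the one analysis in which they are the obvious rival explanation. As written, no analysis separates literacy from education.

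The coefficient is also computed only in patients who chose to fill in one more questionnaire. The article gives patient burden as its reason for accepting selection. That justifies the design, but it does not explain why the selection should go undescribed when rPATD and the covariates are planned for volunteers and non-volunteers alike.

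What is at stake is modest but real. The results are meant to inform later studies, and a correlation that only reflects education could point them in the wrong direction.

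**Working it through.** **Plan's own figure.** There is none to reproduce. The article gives no expected number of volunteers, effect size, significance level or power for the ancillary study. All correlations and coefficients below are assumptions that show orders of magnitude.

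**Step 1: size of a purely confounded correlation.** If literacy (L) has no effect on the rPATD score (R) and education (E) is the only common cause, then r(L,R) = r(E,L) × r(E,R).

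| r(E,L) | r(E,R) | crude r(L,R) |
|---|---|---|
| 0.2 | 0.2 | 0.04 |
| 0.3 | 0.3 | 0.09 |
| 0.4 | 0.3 | 0.12 |
| 0.4 | 0.4 | 0.16 |
| 0.5 | 0.3 | 0.15 |

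These values are on the Pearson scale. A simulation of the 0.4 with 0.3 to 0.4 cases gives a crude Spearman of about 0.115 to 0.15.

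**Step 2: what adjustment does.** The partial correlation is [r(L,R) − r(E,L) r(E,R)] / √{[1 − r(E,L)²][1 − r(E,R)²]}. With 0.4 and 0.3 the numerator is 0.12 − 0.12 = 0. In the simulation, the partial rank correlation given education falls to about 0.006.

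**Step 3: scale against precision.** With standard error √[1.06/(n − 3)] for Fisher's z of a Spearman coefficient, the 95% half-width on the z scale is 1.96 × √(1.06/97) = 0.205 at n = 100, 0.144 at n = 200 and 0.117 at n = 300. A confounded 0.12 to 0.16 is therefore comparable with the sampling uncertainty, and exceeds it if nearly everyone volunteers. A larger sample makes such a signal look firmer without making it more correct.

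**Step 4: what the existing data can do about selection.** One million patients were simulated with no literacy effect and about half volunteering. Age and education affected both literacy and rPATD. The participation weights used age, education and rPATD, because literacy is unknown in non-volunteers.

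| Volunteering depends on | Crude, all | Crude, volunteers | Crude, weighted | Adjusted, all | Adjusted, volunteers | Adjusted, weighted |
|---|---|---|---|---|---|---|
| age, education, rPATD | 0.178 | 0.096 | 0.182 | 0.005 | 0.005 | 0.007 |
| literacy, rPATD | 0.177 | 0.038 | 0.067 | 0.004 | −0.096 | −0.101 |

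The log-odds coefficients were 0.8 (education), −0.5 (age) and 0.8 (rPATD) in the first row, and 1.0 (literacy) and 0.8 (rPATD) in the second.

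In the first row weighting restores the crude value. In the second it recovers (0.067 − 0.038)/(0.177 − 0.038) = 0.029/0.139, about 21% of the loss, and does not improve the adjusted estimate. A second simulation let volunteering depend on literacy and rPATD at 0.8 log-odds per SD each, with a full-sample Spearman of 0.29. It gave 0.16 in volunteers and 0.19 after weighting, a recovery of 0.03/0.13, about 23%.

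**The case against.** The strongest reply is that a rank correlation is a legitimate description of a relationship, that the ancillary objective sets no causal estimand, and that the authors have already disclosed the selection, weighed it against burden and called the results preliminary. This stands in part. It lowers the severity, and it means that the crude coefficient should stay. It does not remove the mismatch with the stated hypothesis of influence.

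A second reply is that a condensed article may leave adjusted analyses to a plan that is not shown. That plan may indeed contain them. But the article states a specific method, so the point concerns the choice it publishes and not an absent detail. The covariate list for secondary objective 1 is introduced as examples, so literacy is not excluded from that model; equally, nothing says that it will enter.

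A reader might infer more than the documents support:

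- **That the data on the 300 could remove confounding and most of the selection bias.** Adjustment handles measured confounders only. Weighting works only if volunteering is independent of literacy given the weighting variables, which cannot be tested here. If willingness to answer a literacy questionnaire depends on literacy, most of the bias remains and the adjusted estimate is itself biased (about −0.10 against a true value near 0 in the second row above).
- **That false-positive rates can be attached to the plan.** The article says that coefficients will be calculated. It sets no test, significance level or number of volunteers for this analysis. Multiplicity across four rPATD factors and three literacy dimensions is a separate matter that adjustment would not address.
- **That rPATD and the covariates are held on all 300.** That number is a recruitment target, and the rPATD is a self-questionnaire in frail patients. Complete data are planned, not assured.

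**Conclusion.** The point holds in a limited form. The only stated analysis of the ancillary objective cannot distinguish literacy from education or age, although the variables needed for a better-targeted estimate are already planned. Under the assumed correlations (0.4 for education with literacy, 0.3 to 0.4 for education with rPATD), a crude correlation of about 0.12 to 0.16 would appear with no literacy effect. With weaker links of 0.2 and 0.2 it would be only 0.04, so the size depends on values that the article does not give.

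The severity is minor: the study is ancillary, voluntary and declared preliminary, and its selection bias is openly acknowledged. The documents do not support saying that the result will be wrong, or that reanalysis would cure the selection problem.

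**What to change.** 1. Keep the crude Spearman coefficients as description, with confidence intervals.
2. Report beside each a partial rank correlation adjusted for age, sex, education and performance status. Equivalently, add the literacy score to the secondary objective 1 linear model, fitted in those who completed the FCCHL/HLS14.
3. Tabulate volunteers against non-volunteers on rPATD and the same covariates, and give the number who took part.
4. If participation weights are used, label them a sensitivity analysis.
5. State that unmeasured confounding and selection on literacy itself cannot be corrected with these data.

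This costs a little analysis time and needs no new data, visits or questionnaires. Intervals widen slightly. With an assumed 100 volunteers and four adjustment terms, the approximate half-width on the z scale goes from 1.96 × √(1.06/97) = 0.205 to 1.96 × √(1.06/93) = 0.209, and a little further if education enters as several categories.
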